### **3 STUDY ENDPOINTS**

#### **3.1 Primary Endpoint**

- 3.1.1 *Feasibility of recruitment and retention of a study sample for a future efficacy trial of MTM-Kids intervention to mitigate food-related insecurities for households of adolescents in active treatment with chemotherapy for pediatric cancer is defined as 70% enrollment, 70% completion of baseline and Week 12 surveys, and 70% receipt of at least 4 weeks of meal deliveries + completion of at least one interview by adolescent and by parent (either week 4, 8 or 12)*

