### **5.4 Participant Replacement**

Participants who provide informed consent, parental permission, or adolescent assent and subsequently withdraw or are removed prior to meeting the requirements of evaluability for the primary endpoint may be replaced to obtain the stated number of evaluable participants for the study.

---

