### **6.3 Participant Withdrawal**

If an adolescent or parent decides to withdraw from the study (and not just from the protocol intervention) an effort should be made to complete and report study assessments as thoroughly as possible. At the time of withdrawal, the investigator should attempt to establish as completely as possible the reason for the study withdrawal.

---

- A complete final evaluation at the time of the participant's study withdrawal should be obtained with an explanation of why the participant is withdrawing from the study.
- If the participant is noncompliant and does not show up for an end of study follow up assessment, this should be documented in the eCRF.

Excessive participant withdrawals from protocol intervention or from the study can render the study not feasible therefore, unnecessary withdrawal of participants should be avoided.

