## 8 STATISTICS

We will calculate descriptive statistics (frequency, proportion, central tendency, range, standard deviation [SD], reliability) to describe the study sample and estimate proportions, odds ratio, and confidence intervals (CI) for a priori feasibility benchmarks (see Time & Events Table). Feasibility study data can provide unreliable effect size estimates given small sample sizes. [46, 58] Thus, we will follow Brown [59] and estimate SDs and CIs for signals of change in food-related insecurities, cost-coping, time demands and QOL and use upper limits of 80% CIs plus enrollment and retention data to estimate sample size for the future efficacy trial. We will also consider evidence for associations between improvement in food security and QOL from studies of MTM with adult populations in estimating sample size for the future trial. [11, 44] Within days of an interview, two coders per interview will use rapid qualitative content analysis to analyze verbatim transcripts, compare their results and engage in discussion to resolve any discrepancies. The conceptual model (Figure 1) will guide the rapid analysis.[60] The goal is to identify actions at multiple levels (meal, child, household, study) to inform refinements for validation testing and ultimately the protocol for the future trial. When all interviews have been completed, we will use traditional content analysis to identify themes in the data overall to inform further refinements.

To ensure a rigorous and reproducible study, we have taken the following steps:

- Established a plan to enroll a diverse sample
- Justified the sample size
- Selected established measures to measure study variables
- Established the data analysis plan prior to data acquisition
- Considered relevant biological variables

Because sex hormones can affect taste function, processing of sweet and bitter, and food acceptability, [61] we will enroll similar numbers of biological female and male adolescents for each aim and explore the role of biological sex in the quantitative and qualitative data about alterations in taste and meal acceptability.

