### 8.1 Study Design

This feasibility study uses a longitudinal design and multiple methods to determine the possibility of using the MTM-Kids study processes and intervention in a future full-scale RCT. 15 parent/adolescent dyads will be enrolled and asked to complete a survey at baseline (T1), receive MTM-Kids meals over 12 weeks, participate in interviews at 4, 8, and 12 weeks (T2, T3, T4) after starting to receive meals to inform refinement, and complete a follow-up survey at 12 weeks (T4).

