### **8.2.2      *Total Accrual***

The total accrual will be 30 (15 adolescents + 15 parents).

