## **8.3      Data Analysis Plans**

### **8.3.1      *Primary Endpoint Analysis***

For project to be considered successful and feasible in a larger study, we determined the following benchmarks: a) 70% of those approached are enrolled in the study, (b) 10 out of 15 participating parent/adolescent dyads should complete the baseline and week 12 surveys, (c) 10 out of 15 parents receive at least 4 weeks of meal deliveries, and (d) in 10 out of 15 dyads, the adolescent and the parent each complete at least one interview (week 4, 8, or 12). We will estimate the retention rate and report it with a 95% confidence interval.

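### Section 5.4 allows early leavers to be replaced although the primary endpoint is retention, so failures can fall outside the 10-of-15 benchmarks and the reported retention rate

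*Protocol*

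**What the plan says.** Protocol section 5.4 covers people who give consent, permission or assent and then leave. Those who "withdraw or are removed prior to meeting the requirements of evaluability for the primary endpoint may be replaced to obtain the stated number"; the number meant is that of evaluable people. The protocol does not define evaluability for the primary endpoint.

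That endpoint (section 3.1) is feasibility of recruitment and retention. Besides enrolment it requires "70% completion of baseline and Week 12 surveys, and 70% receipt of at least 4 weeks of meal deliveries", together with at least one interview by the adolescent and one by the parent. Section 8.3.1 turns this into benchmarks. Benchmark (b) reads "10 out of 15 participating parent/adolescent dyads should complete the baseline and week 12 surveys"; (c) on meal deliveries and (d) on interviews use the same 10 out of 15. The section adds: "We will estimate the retention rate and report it with a 95% confidence interval".

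Section 8.1 says that "15 parent/adolescent dyads will be enrolled", and section 8.2.2 sets total accrual at 30 people, which is 15 dyads with no allowance for replacements. Section 6.3 warns: "Excessive participant withdrawals from protocol intervention or from the study can render the study not feasible". Section 8 plans to "use upper limits of 80% CIs plus enrollment and retention data to estimate sample size for the future efficacy trial".

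**The concern.** Replacing participants until a set number is evaluable can be reasonable when the endpoint is something that only people who stay can supply. Here the endpoint is staying. A family that consents and withdraws before week 12 has given a complete answer to the primary question, and the answer is no. Under 5.4 that family can be treated as not yet evaluable and another enrolled in its place.

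Once anyone is replaced, more than 15 dyads have been enrolled. The 15 in benchmarks (b) to (d) can then no longer be all enrolled dyads, and the natural reading is the 15 evaluable ones. The outcome being measured would then help decide who is counted. The withdrawals that section 6.3 calls a threat to feasibility are the ones that could disappear from the result. Section 6.1 lets staff end the intervention for non-compliance or on the investigator's judgement, so the group at issue may also include dyads removed by staff.

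Two decisions depend on the figure: whether the project counts as feasible for a larger study (8.3.1), and how many families the efficacy trial plans to enrol (8).

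**Working it through.** **Inputs from the protocol.** Pass mark 10, denominator 15 (8.3.1); 15 dyads enrolled (8.1, 8.2.2). The sample size was set on logistic grounds and on usability-testing evidence (8.2.1), so there is no power calculation to reproduce.

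**Inputs assumed.** The protocol states neither a completion rate nor a withdrawal rate. Below, *k* is the number of dyads replaced and *p* the true completion rate among all enrolled dyads. Both are assumptions.

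**Step 1. The same ten completers over two denominators.** The rate is 10/(15 + k), with Clopper-Pearson 95% intervals. The last column is 100 divided by the rate: the number of families to enrol for 100 completers if the next trial planned from the point estimate.

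| Dyads replaced | Enrolled | Rate among enrolled | Exact 95% CI | Enrol per 100 completers |
|---|---|---|---|---|
| 0 | 15 | 66.7% | 38.4% to 88.2% | 150 |
| 1 | 16 | 62.5% | 35.4% to 84.8% | 160 |
| 2 | 17 | 58.8% | 32.9% to 81.6% | 170 |
| 3 | 18 | 55.6% | 30.8% to 78.5% | 180 |

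If replaced dyads are left out, every row is reported as 10/15, 66.7%, and passes.

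**Step 2. Chance of passing one 10-of-15 benchmark.** If a share r = k/(15 + k) of enrolled dyads are non-completers who are replaced and not counted, the completion rate among the 15 counted is p/(1 − r). For example, with p = 0.50 and k = 3, r = 3/18 = 0.167 and the counted rate is 0.50/0.833 = 0.60. The pass probability is the exact binomial P(X ≥ 10) with n = 15.

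| True rate p | No replacement | k = 1 | k = 2 | k = 3 |
|---|---|---|---|---|
| 0.50 | 15.1% | 22.0% (rate 0.533) | 30.5% (0.567) | 40.3% (0.600) |
| 0.60 | 40.3% | 53.2% (0.640) | 66.1% (0.680) | 77.8% (0.720) |

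**Step 3. A heavier assumption.** Suppose a share f of all failures are early and replaced. The counted rate is p/(1 − (1 − p)f). With f = 0.5 and p = 0.50 this is 0.50/0.75 = 0.667, and the chance of passing is 61.8% against 15.1%. On average 15/0.75 = 20 dyads would be enrolled to fill the 15 places.

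**Direction.** Dropping non-completers leaves the completers unchanged and shrinks the denominator, so whatever *p* and *k* are, the apparent rate can only rise.

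**The case against.** The strongest reply is that 5.4 governs accrual, not analysis. It allows a substitute to be enrolled and does not say that the departed dyad leaves the denominator. An analyst could replace a dyad and still count it as not retained without breaking any sentence in the protocol. Defining the analysis set is often left to a statistical analysis plan, which is not at hand. Evaluability might also mean something modest, such as having completed baseline; then only very early exits could be replaced and later dropouts would count as failures.

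Several further points narrow the concern. The sample size was chosen to gather usability feedback, and a dyad that leaves before giving any adds little to that aim, so replacement has a legitimate purpose. Reasons for stopping and withdrawing are to be documented (6.1, 6.3). A dyad that merely skips the week 12 survey has neither withdrawn nor been removed, so 5.4 does not reach it. Counting a dyad stopped because the child's condition changed as a retention failure is a design choice.

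Much of this stands as a limit on size and certainty. It does not remove the problem. Replacement is a protocol rule applied during enrolment, and the protocol itself fixes both the pass mark and the 15. Those rules do not fit together once a dyad is replaced, and no sentence keeps that dyad in the count. The reply is also right that the next trial's enrolment need not rest on the bare point estimate, since section 8 brings in other inputs. The figures per 100 completers show what could follow, not what must.

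**Conclusion.** The concern holds. Read together, 5.4, 8.1, 8.2.2 and 8.3.1 permit dyads that failed the primary endpoint to be replaced and left out of benchmarks (b) to (d) and of the retention rate with its interval.

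With one to three replacements, a reported 66.7% would correspond to between 62.5% and 55.6% of enrolled dyads. Under the same assumption the chance of passing a benchmark rises from 15% to between 22% and 40% at a true completion rate of 50%, and from 40% to between 53% and 78% at 60%. These probabilities rest on assumed withdrawal and completion rates and on replaced dyads not being counted. The direction of the bias depends only on the latter.

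Replacement is optional, it applies only to exits before an undefined point of evaluability, and benchmark (a), enrolment among those approached, is not affected. The plan should be changed, and before results are known, because the choice of denominator could by itself decide pass or fail.

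**What to change.** Add one sentence to each of 5.4 and 8.3.1: every enrolled dyad, including those that withdraw and those stopped by staff under 6.1, stays in the denominator for benchmarks (b) to (d) and for the retention rate and its 95% confidence interval, and is not replaced for those purposes. If the team wants dyads stopped for clinical deterioration shown separately, they can be reported as a subgroup of the failures.

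Allow extra dyads for interview feedback only, report them outside the benchmarks, and raise the accrual number in 8.2.2 to match. This keeps the formative purpose of the sample.

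The cost is a small text change and a possibly less favourable retention figure. Each extra dyad would need up to 12 weeks of meals and up to $150 in gift cards (4.2), which a replacement under the current 5.4 would cost as well.

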## **5.5 Inclusion of Women and Minorities**

The total number of subjects involved in the study will be 30, including 15 adolescents and 15 parents. Of those, we estimate that approximately 50% will be females. The estimated racial/ethnic breakdown of the study may approximately be that 15% may be Black or African American, 4% may be Asian or Native Hawaiian-Pacific Islander. Approximately 18% of the subjects may be Hispanic. While this provides only an estimated breakdown of the study population, efforts will be made to ensure equitable recruitment of individuals that meet the above eligibility requirements. Participants who identify as African American or Hispanic may be over-represented in the study sample compared to the clinical population - children who are African American or Hispanic are 2-3 times more likely to live in households with food insecurity than non-Hispanic White children [26].

## **6 STUDY CONDUCT**

### **6.1 Duration of Intervention**

Intervention may continue for 12 weeks or until:

- Either the adolescent or parent decides to withdraw from study treatment.
- General or specific changes in the child's condition render them unacceptable for further participation in the judgment of the investigator.
- Significant study intervention or activity non-compliance.

If the subject is removed from the intervention, the Principal Investigator should be notified. The reason for discontinuation of a protocol intervention will be documented in the medical records and on the eCRF. In the case where an adolescent or parent decides to prematurely discontinue protocol intervention ("refuses intervention"), the adolescent or parent should be asked if they may still be contacted for further scheduled study assessments. The outcome of that discussion should be documented in the medical records and in the eCRF.

### **6.2 Duration of Follow-up**

Subjects will not be followed after completion of the final survey.

### **6.3 Participant Withdrawal**

If an adolescent or parent decides to withdraw from the study (and not just from the protocol intervention) an effort should be made to complete and report study assessments as thoroughly as possible. At the time of withdrawal, the investigator should attempt to establish as completely as possible the reason for the study withdrawal.

---

- A complete final evaluation at the time of the participant's study withdrawal should be obtained with an explanation of why the participant is withdrawing from the study.
- If the participant is noncompliant and does not show up for an end of study follow up assessment, this should be documented in the eCRF.

Excessive participant withdrawals from protocol intervention or from the study can render the study not feasible therefore, unnecessary withdrawal of participants should be avoided.

## 6.4 Participants Lost to Follow-up

A participant will be considered lost to follow-up if they fail to return for three scheduled study visits and is unable to be contacted by the study site staff.

The following actions must be taken if an adolescent or parent participant doesn't show up for a required study data collection:

- The site will attempt to contact the parent and reschedule the missed visit and counsel the subject on the importance of maintaining the assigned visit schedule and ascertain if the participant wishes to and/or should continue in the study.
- Before a participant is deemed lost to follow-up, the investigator or designee will make every effort to regain contact (where possible, 3 telephone calls and, if necessary, a certified letter to the participant's last known mailing address or local equivalent methods). These contact attempts should be documented in the child's medical record or study file.
- Should the parent continue to be unreachable, they will be considered to have withdrawn from the study with a primary reason of lost to follow-up.

## 6.5 Off-Study Criteria

Participants will be considered off study and no longer be followed on the protocol for any reason if any of the following criteria are met:

- When the child-parent dyad reaches the end of the study as defined by the [Time & Events Table](#)
  - Either member of the dyad withdraws consent for treatment and any further data collection
  - Death
  - Lost to follow-up (refer to section [6.4](#))
-

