#### **3.2 Secondary**

- 3.2.1 *Participant-reported acceptability, appropriateness, feasibility, affordability, and accessibility of the MTM-Kids intervention is defined as mean overall scores for the 4 item measures of each domain (appendix X)  $\geq 3$  (agree) for 70% of adolescents (acceptability and appropriateness) and 70% of parents (acceptability, appropriateness, feasibility, affordability, and accessibility) at week 12 (T4).*

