### Footnotes to Time & Events Table

1. Screening includes tests to confirm eligibility.
2. Informed consent will include (a) adult consent from the parent for their participation in the study, (b) parental permission for their adolescent's participation, and (c) adolescent assent. HIPAA authorization to extract a

limited set of data from the adolescent's electronic medical record. Completion of the parent contact form, baseline assessments and Equiti Food account set-up will commence after the written consent/permission/assent have been obtained.

3. Parent participants must register with the Equiti Foods Website in order to select and order MTM allotment. Allotment will be weekly (up to 10 meals per week), for 12 weeks. Delivery will take 3-5 days and parents can order up to 5 working days in advance.
  4. Adolescents will complete surveys at baseline, T2, T3 and T4. See [ADOLESCENT SURVEYS](#)
  5. Parents will complete surveys at baseline and at 12 weeks (T4). See [PARENTAL SURVEYS](#)
  6. A limited set of data (specified in the HIPAA authorization form) about the adolescent's cancer diagnosis, diagnosis date, treatment protocol, treatment initiation date, and treatment exposures to date will be extracted from the adolescent's electronic medical record.
  7. Gift cards will be given following completion of the Baseline and then the 12-week survey, and following completion of the Week 4, 8 and 12 interviews. The gift cards value will be \$15 for parent and \$15 for the child, for a possible total of \$75 for parent and \$75 for child.
  8. Parents will be contacted within 1 week following baseline data collection to verify that they have placed the initial meal order, and problem-solve as indicated.
  9. Semi-structured interviews will be conducted and audio-recorded via an IRB-approved secure video platform, or in-person during a regularly scheduled clinical visit according to the participant's preference. An investigator-developed interview guide will inform the interviews (see [APPENDIX III – Study Semi-Structured Interview Guides](#)).
-

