### 15.3.2 Adolescent Interview Guide

Thank you for talking with me today about the MTM Kids research study – that's the frozen meals being delivered to your family. We want to find ways to help kids going through chemo and their families have meals that are easy to prepare. You are in the MTM-Kids study, which is looking at a new way of helping families during treatment. We want to make the MTM program works for kids like you. We ask for your thoughts about one of the frozen meals you tried. We also ask for your advice about how to make the frozen meals better for kids and their families. We value your input and saying yes to this study.

I am part of the MTM Kids research team. I'm not a part of the team taking care of you. I am talking with you to learn what about MTM Kids is and is not working for kids going through chemo so the study team can make the meals better for kids.

1. To start, please show me or take a share a picture/show us a MTM-Kids meal you tried. **Probe on:**

[if they haven't tried any] Please tell me about why you haven't tried a meal yet. Now, please tell me about something else you ate recently.

2. How did that meal/food work for you? **Probe on:**

- a. How was the taste for you – too spicy, not spicy enough?
- b. How was the smell?
- c. How was the amount – too much, not enough?
- d. Did someone heat it up for you, or did you do it yourself?

[if by self] How was that for you?

---

3. What are your ideas about how we can make the frozen meals better for kids going through chemo? **Probe on:**

- a. More /less spice?
- b. Smaller/larger portions?
- c. Add more meal types?

[if more types] What ideas do you have about new meals or other things to eat that kids going through chemo would enjoy?

4. When you think about your family's needs right now for healthy, easy to prepare food right now, can you describe how MTM Kids does and doesn't help address those needs? **Probe on:**

- c. What specific changes would you like to see in MTM Kids to make it better?
- d. Who is ordering the MTM Kids meals?

[if the adolescent]

- a. About how often are you doing that?

[If less often than weekly] What influenced your ordering meals less often than weekly? **Probe on:**

- c. Number of meals, meal size/portions, meal types, freezer space?
- d. How difficult or easy has it been to order meals online?

[If number of meals, portions, types, space] what ideas do you have about how we could to improve X

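### Section 6.5 ends follow-up of both dyad members when one fully withdraws consent, which discards week-12 data from a partner who is still willing

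*Protocol*

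**What the plan says.** Section 6.5 opens with "Participants will be considered off study and no longer be followed on the protocol for any reason" and then lists the triggers. One of them is "Either member of the dyad withdraws consent for treatment and any further data collection". The consequence is stated for participants in the plural, and nothing is said about the member who has not withdrawn.

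Section 6.1 deals with stopping the intervention, which is a different event. It gives three grounds: "Either the adolescent or parent decides to withdraw from study treatment", a change in the child's condition as judged by the investigator, and "Significant study intervention or activity non-compliance". For a stop chosen by a member, "the adolescent or parent should be asked if they may still be contacted for further scheduled study assessments". For the other two grounds, 6.1 asks that the Principal Investigator be notified and the reason recorded, and does not mention later assessments.

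Three other places bear on the point:
- The footnotes to the Time & Events Table separate the parent's own consent, "adult consent from the parent for their participation in the study", from parental permission and from the adolescent's assent.
- Section 3.2 sets one 70% threshold for adolescents and another for "70% of parents (acceptability, appropriateness, feasibility, affordability, and accessibility) at week 12 (T4").
- Section 3.3.1 defines the exploratory signals as change from T1 to T4. Section 7.2.2 shows that all five of these measures come from the parent survey.

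**The concern.** The unit of the off-study rule does not match the unit of the data. The rule works on the dyad. The secondary endpoint and the exploratory measures work on the individual, and mostly on the parent: parents supply five of the seven domain ratings and all five T1-T4 outcomes. None of these needs anything from the adolescent.

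Suppose an adolescent withdraws assent fully at week 6. On the wording of 6.5, the parent is no longer followed. The parent's own week-12 survey and remaining interviews are not collected, even if the parent wants to give them. The reverse also holds: if the parent withdraws their own consent but leaves permission for the adolescent in place, the adolescent's week-12 ratings go too.

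Two things are at stake. One is precision in a study of 15 dyads, where section 8 plans to use standard deviations and 80% confidence limits for change to help size the efficacy trial. The other is selection. Families in which one member has withdrawn may differ from those that stay intact, and their views are among those a feasibility study would want to hear.

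**Working it through.** **Reading the rule.** The trigger is withdrawal from both the intervention and data collection, by either member. The consequence is the end of follow-up for participants. No clause preserves the other member's data collection. Section 6.3 asks for a final evaluation, but of the withdrawing participant and at the time of withdrawal, so it is not the partner's T4 measurement. Section 5.4 may restore the number of dyads, but a replacement dyad does not bring back the lost partner's answers.

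**Inputs.** 15 dyads, 15 × 2 = 30 participants, which agrees with the total accrual in 8.2.2. No withdrawal rate is given, so every rate below is an assumption.

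**Precision, simple illustration.** Assume a constant standard deviation, no replacement, and a willing parent in each affected dyad. The standard error of a mean change is proportional to 1/√n.
- 3 full adolescent withdrawals: parents fall from 15 to 12, factor √(15/12) = 1.12.
- 5 full adolescent withdrawals (the number of dyad failures that 8.3.1 tolerates, 15 − 10): parents fall from 15 to 10, factor √(15/10) = 1.22.

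**Precision over a range of rates.** Let each member fully withdraw independently with probability w. Expected dyads off study = 15[1 − (1 − w)²]. Expected willing partners removed, of 30 participants = 30w(1 − w). Expected week-12 respondents per role = 15(1 − w)² under the dyad rule and 15(1 − w) under a per-participant rule.

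| w | Dyads off study | Willing partners removed | Per role, dyad rule | Per role, individual rule |
|---|---|---|---|---|
| 5% | 1.5 | 1.4 | 13.5 | 14.25 |
| 10% | 2.9 | 2.7 | 12.2 | 13.5 |
| 15% | 4.2 | 3.8 | 10.8 | 12.75 |
| 20% | 5.4 | 4.8 | 9.6 | 12.0 |

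The ratio of the last two columns is 1/(1 − w), so the rule itself costs a standard-error factor of about √[1/(1 − w)]: 1.05 at 10% and 1.12 at 20%. If the two members of a family tend to withdraw together, fewer willing partners are lost than shown.

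**Direction.** Section 3.2 does not say how a parent with no T4 rating counts towards the 70%, so the effect can go either way.
- If only responders count: 10 of 15 parents favourable is 67%, below 70%. Remove three of the five unfavourable parents and it becomes 10/12 = 83%, above it.
- If a missing parent counts as not meeting the threshold: 11 of 15 favourable is 73%, above 70%. Remove one favourable parent and it becomes 10/15 = 67%, below it.

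**Primary benchmarks.** Benchmark (b) in 8.3.1 needs both members' baseline and week-12 surveys. A dyad with one member withdrawn before week 12 fails it under either rule, so the count does not change. Benchmark (d) could differ only where the withdrawn member had already been interviewed and the partner had not.

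**The case against.** The strongest reply is that linking the two members is a defensible choice. A parent qualifies only as caregiver of an eligible adolescent, much of the parent interview concerns the child's care, and a family may prefer a clean end when an adolescent refuses further contact. That is a fair reason not to press anyone. It is not a reason to bar a parent who still consents from completing a survey about household food, finances and the meals.

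Several stronger readings are tempting, and the protocol does not support them:
- *Any withdrawal ends follow-up.* It does not. A member who stops only the meals stays on study and is to be asked about further assessments. A family that merely dislikes the meals need not trigger 6.5.
- *Investigator-initiated stops end data collection.* Section 6.1 is silent here, and 6.5 does not list such removal. These dyads remain on the Time & Events schedule, and 6.4 requires attempts to recontact and reschedule after a missed data collection. One could compute benchmark (b) falling from 11/15 (73%) to 9/15 (60%) if two such dyads were not surveyed, but no section says they would not be.
- *The study loses the reasons for failure.* Sections 6.1 and 6.3 require the reason for discontinuation or withdrawal to be sought and recorded.
- *The results are biased upward.* Plausible, but not shown. It depends on who withdraws and on how missing ratings are counted.
- *The non-compliance ground contradicts the interview guide.* The adolescent guide provides for non-users ("if they haven't tried any] Please tell me about why you haven't tried a meal yet"), but meals are offered as a weekly maximum, and low use is nowhere defined as significant non-compliance.

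Replacement under 5.4 also weakens the precision argument, since numbers may be made up. It does not answer the selection argument.

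**Conclusion.** The point holds in a narrow form. Section 6.5, as written, stops data collection from a separately consented participant because the other member has fully withdrawn. The loss falls on the week-12 secondary endpoint and on the parent-reported T1-T4 measures. The primary survey benchmark is untouched.

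The size is modest and uncertain. The factors of 1.12 and 1.22 assume three or five full adolescent withdrawals, a willing parent each time, and no replacement; the protocol supplies no rate against which to judge how likely that is. The loss may be selective, but neither its direction nor its size can be established from the document. The silence in 6.1 after investigator-initiated stops is an ambiguity to clear up, and should not be read as a rule that discards data. This is an inexpensive improvement to a stated rule. It does not threaten the study's main conclusion.

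**What to change.** In 6.5, apply off-study status to each participant for data collection. After an adolescent withdraws assent, a parent who still consents completes their own remaining surveys and interviews. Withdrawal of parental permission still ends the adolescent's participation. The dyad still counts as a failure on the dyad-level benchmarks it had not already met at the time of withdrawal.

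As a secondary clarification, reconcile 6.1 with 6.5 by stating that scheduled assessments continue after any stop of the intervention, whoever initiated it, unless consent for data collection is withdrawn. This concerns data collection only; no change to the grounds for stopping the intervention is proposed.

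The cost is a sentence in each section, a line in the consent form, and a few extra contacts. The contacts need tact, because they are with families in which one member has chosen to leave. The surveys and interviews are already part of the planned schedule.
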